### Data analysis

The data analyses will be performed with the “IBM SPSS Statistics 21” software. In order to be able to assess the quality of the randomisation, the baseline data from the intervention and control groups will be examined for statistically significant differences. All data will be checked for plausibility. Patients who drop out of the study but are still available for the telephone interviews are being interviewed subsequently. A missing data evaluation will be carried out, and missing values will be imputed by EM-Imputation [62]. The main outcome criterion is severity of depression assessed by the MADRS. The primary data analytic strategy is “per protocol” for the superiority trial and “intention to treat” for the non-inferiority trial [63]. As a sensitivity analysis, an additional analysis with “intention to treat” for hypothesis 1 and “per protocol” for hypothesis 2 will be performed. The level of statistical significance is set at *p* = 0.05.

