### Sample size estimation

A power analysis was computed on the basis of the authors’ previous experience with the BPT in the pilot study in which a Cohen’s d of 0.77 was reached [33]. To address Hypothesis I, a slightly lower effect size of 0.6 was assumed. Thus,61 patients will be needed in the BPT group and 61 patients in the EP group (alpha = .05, power = .9).

To address Hypothesis II, a non-inferiority margin of 1.9 points (SD = 3.8) on the PHQ-9 (as proposed in the literature [36]) was used, which resulted in a total of 69 patients in the BPT group and 69 patients in the CBT group (alpha = .05, power = .9). Thus, there should be 61 patients in the EP group, 69 patients in the BPT group, and 69 patients in the CBT group, for a total of 199 patients. To account for dropouts between t0 and t1, 20% more patients are added (based on the drop-out-rate of our pilot study), resulting in 40 additional patients for a total of 239.

Therefore, 10 waves in three therapy centres (two waves in Berlin, four waves in Weyarn, four waves in Erlangen) were planned. Each wave was designed to include 24 participants on average, of which 20 were expected to complete the respective intervention.

Also from the data of the pilot study, in which similar recruitment modalities were applied, a failure of approx. 40% of patients who do not meet the inclusion criteria must be expected. This means that a total of approximately 400 patients should be screened.

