## Abbreviations

ADHD: Attention deficit hyperactivity disorder
BMI: Body mass index
BPT: Bouldering psychotherapy
CATI: Computer-assisted telephone interview
CBT: Cognitive behavioural therapy
EM-Imputation: Imputation using an expectation maximization algorithm
EP: Exercise program
EQ-5D: EuroQol Five Dimension Questionnaire
FERUS: Questionnaire on Resources and Self-Management Skills
FKB-20: Body Image Questionnaire
GAD-7: Generalized Anxiety Disorder 7
GSE: General Self-Efficacy Scale
HRQoL: Health-related quality of life
MADRS: Montgomery-Asberg Depression Rating Scale
PHQ-9: 9-Item Patient Health Questionnaire
R-SES: Rosenberg Self-Esteem Scale
SAE: Severe adverse events
SCL-90: Symptom-Checklist
SD: Standard Deviation
SIGMA: Structured interview guide for the Montgomery-Asberg Depression Rating Scale
UIAA scale: Scale of difficulty of the Union Internationale des Associations d’Alpinisme (International Union of the Alpine Associations)
VAS: Visual analogue scale

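### Missing scores are filled in by EM imputation and then tested as if observed, which raises false non-inferiority above 5% in the intention-to-treat comparison with CBT

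*Protocol article*

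**What the plan says.** All places are in the Methods of the protocol article unless stated.

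- Data analysis: "missing values will be imputed by EM-Imputation". The abbreviation list explains the term only as "Imputation using an expectation maximization algorithm". The software is fixed too: "The data analyses will be performed with the “IBM SPSS Statistics 21” software".
- Data analysis, analysis sets: "The primary data analytic strategy is “per protocol” for the superiority trial and “intention to treat” for the non-inferiority trial". The planned sensitivity analysis exchanges the two sets and leaves the missing-data method unchanged.
- Data analysis, follow-up: "Patients who drop out of the study but are still available for the telephone interviews are being interviewed subsequently". An evaluation of missing data is also announced.
- Sample size estimation: "To account for dropouts between t0 and t1, 20% more patients are added", "resulting in 40 additional patients for a total of 239".
- Hypothesis I and Hypothesis 2: t-tests on change scores, ANOVA and regression for superiority. Non-inferiority is judged against 1.9 points on the PHQ-9 and against Cohen's d of 0.2 and 0.34 on the MADRS.

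The article does not list the variables in the imputation model. In particular, it does not say whether treatment arm is among them.

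**The concern.** EM imputation replaces a missing score by a value predicted from the observed data. A t-test or confidence limit computed on the completed data then treats that prediction as a measurement, and the uncertainty of the prediction is lost. What follows depends on the imputation model:

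- **Arm in the model.** The group difference is unbiased, but its standard error is too small.
- **Arm not in the model.** Patients with missing scores get the same prediction in every arm, so the arms are pulled together. In a superiority test this costs power. In a non-inferiority test it favours the claim.

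The claim that BPT is not inferior to CBT rests primarily on the intention-to-treat set, where filled-in values enter directly.

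**Working it through.** **Inputs from the article.** PHQ-9 margin 1.9 and SD 3.8, so 1.9/3.8 = 0.50 SD; MADRS margins 0.34 and 0.2 SD; 69 per arm, alpha .05, power .9; 199 enlarged to 239.

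**Assumptions.** Baseline-outcome correlation r = 0.5, scores missing completely at random, t1 only. The article gives none of these.

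**The plan's own figure.** n = 2(1.645 + 1.282)² × (3.8/1.9)² = 68.5, so 69 per arm. This reproduces with a one-sided 5% test, so 5% is the nominal false non-inferiority rate. With the allowance, 69 × 1.2 is about 83 per arm. The missing share is 40/239 = 16.7% if every dropout lacks a t1 score; 20% is shown as an upper figure.

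**Arm in the model.** For a missing share m:

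- reported SE = 3.8 × √[(2/83)(1 − m(1 − r²))]
- true SE = 3.8 × √[(2/83)(r² + (1 − r²)/(1 − m))]

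At m = 0.20 these are 3.8 × √(0.0241 × 0.85) = 0.544 and 3.8 × √(0.0241 × 1.1875) = 0.643, a ratio of 0.846. False non-inferiority is Φ(−1.645 × 0.846) = 8.2%. Two-sided superiority error is 2Φ(−1.96 × 0.846) = 9.7%. The ratio does not depend on the number per arm, so it also serves for BPT against EP.

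With all 83 patients per arm observed, the SE would be 3.8 × √(2/83) = 0.590. The filled-in data thus claim more precision (0.544) than complete follow-up would give.

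**Arm omitted.** The difference is estimated as (1 − m) times its true size. At m = 0.20, 1.9 becomes 1.52. False non-inferiority is Φ(m × margin/SE − 1.645) = Φ(0.38/0.544 − 1.645) = 17.2%.

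| Missing | Reported SE | True SE | False NI, arm in | Superiority error (ITT), arm in | False NI, arm omitted: 0.50 / 0.34 / 0.20 SD |
|---|---|---|---|---|---|
| 20% | 0.544 | 0.643 | 8.2% | 9.7% | 17.2 / 12.1 / 8.6% |
| 16.7% | 0.552 | 0.633 | 7.6% | 8.8% | 14.3 / 10.5 / 7.9% |
| 10% | 0.567 | 0.614 | 6.4% | 7.0% | 9.5 / 7.8 / 6.5% |
| 5% | 0.579 | 0.601 | 5.7% | 5.9% | 6.9 / 6.3 / 5.7% |

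**Simulation (83 per arm, r = 0.5, 16.7 and 20% missing).** It agrees with the formulas:

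- Arm in: false non-inferiority 7.6 and 8.5% on t1 scores, 7.1 and 7.9% on change scores.
- Arm omitted: 14.0 and 18.2% on t1 scores, 13.9 and 16.5% on change scores. Superiority error stays at 4.7 to 5.1%.
- Multiple imputation with arm (20 datasets, Rubin's rules): 4.3 to 4.8%.

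Over correlations from 0 to 0.7, the SE shortfall with arm in is about 10 to 20% and false non-inferiority is 6.4 to 9.9%. With arm omitted it is about 13 to 19% at the PHQ-9 margin. Adding one random residual to each single fill-in does not cure this: superiority error with arm in was still 9.1%.

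**MADRS margins in Cohen's d.** If d is standardised by the SD of the filled-in data, that SD is too small by the factor √0.85 = 0.922 at m = 0.20, so d is enlarged and part of the error is offset. The nominal SE of d is √(2/83) = 0.155. With arm in, its true SE is (0.643/3.8)/0.922 = 0.1835.

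- Arm in, margin 0.34: Φ[(0.34 − 0.369 − 1.645 × 0.155)/0.1835] = 6.1%. Margin 0.2, with d = 0.2/0.922 = 0.217: 6.9%.
- Arm omitted, margin 0.34: Φ[(0.34 − 0.8 × 0.369 − 0.255)/0.155] = 8.8%. Margin 0.2: 7.0%.

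The PHQ-9 margin is in raw points and has no such offset.

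**The case against.** Four objections carry weight.

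1. **Both hypotheses are not equally affected.** A reader might infer that the error of the superiority test is inflated as well. The article does not support that as a general statement. Superiority is primarily analysed per protocol, where patients who do not complete treatment, and who would carry most imputed values, largely fall outside the set. If arm is omitted, superiority error stays near 5%. The 8.5 to 10% figure belongs to the intention-to-treat sensitivity analysis, and only with arm in the model.
2. **Twenty per cent missing is not what the article predicts.** The allowance amounts to 16.7% of those randomised, and dropouts who can be reached are still interviewed, so dropout is not the same as a missing score. The article gives no lower rate; the 10 and 5% rows are assumed.
3. **The largest figures are conditional.** A reader might take the 14 to 18% as an established error of the plan. It holds only if arm is left out, and the imputation variables may properly be set out in a fuller document.
4. **The article does not use the word single.** That is a reading of a named fill-in method with no mention of several datasets or pooling.

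What remains after these points is that a method is named which does not carry imputation uncertainty into the tests that follow. Each choice of imputation model examined leaves false non-inferiority above 5%, and the planned sensitivity analysis does not vary the method.

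**Conclusion.** The point holds for the intention-to-treat analyses, above all the primary non-inferiority comparison with CBT. At 16.7 to 20% missing, false non-inferiority is about 7 to 9% with arm in the model. With arm omitted it is about 14 to 18% at the PHQ-9 margin, 11 to 13% at 0.34 SD and 8 to 9% at 0.2 SD, all against 5%. On the Cohen's d scale planned for the MADRS the excess is smaller, at about 6 to 9% for 20% missing. At 10% missing the raw-scale rates fall to about 6 to 10%, and at 5% to about 5.5 to 7%.

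The mechanism is certain. The sizes rest on an assumed correlation of 0.5, data missing completely at random, and t1 only. Dropout related to outcome could add bias that is not quantified here. The direction favours the non-inferiority claim, so the method should be changed before analysis.

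**What to change.** For the t1 analyses, replace EM fill-in by one of the following:

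- multiple imputation with treatment arm in the imputation model, at least 20 datasets, combined by Rubin's rules; or
- a likelihood-based mixed model on the observed scores. Where EP is compared, restrict it to t0 and t1, because the section on the exercise program offers EP participants a bouldering group after the second measurement, and later EP scores may then reflect BPT.

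For the non-inferiority analysis, add a sensitivity analysis that worsens imputed BPT values in steps from zero up to the margin, and report where the conclusion changes.

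The cost is some extra analysis work and wider intervals. At the planned missingness, multiple imputation gives an SE of about 0.64 to 0.65, where EM with arm in the model reports 0.54 to 0.55. This loses nothing against the plan: 69 completers per arm imply 3.8 × √(2/69) = 0.647, the precision on which the sample size was based.

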#### Research hypothesis

I.Bouldering psychotherapy (BPT) leads to a significantly greater reduction in depressive symptoms in outpatients with depression than mere physical activity in the form of a home-based exercise program (EP).II.The positive effect of bouldering psychotherapy (BPT) on reducing depressive symptoms in outpatients with depression is not inferior to the effect of cognitive-behavioural psychotherapy (CBT).

In this article, we describe the StudyKuS study protocol, which serves as a reference for forthcoming papers that report the results of the study.

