#### Exercise program (EP)

The home-based Exercise Program consists of a 20-min physical training program, which addresses the same muscles used in bouldering or climbing. At the beginning of the intervention, all participants receive a training manual (including instructions and explanations of all of the exercises), a training DVD, training material (e.g. a multifunctional latex band and training rings to enhance finger and underarm power), as well as psychoeducational material explaining the link between physical activity and mood. Participants are instructed to engage in the training program on their own at home approximately three times a week for the study period of 10 weeks. They receive reminders via e-mail to motivate them to keep on exercising. At the midpoint of the intervention (5 weeks), they are sent additional motivational material via postal mail. After 10 weeks, participants are asked how often they conducted the exercises. After the second measurement point, former EP participants are offered the opportunity to participate in a subsequent 10-week bouldering group, which follows the same treatment plan as the BPT group.

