## Discussion

This is the first study to investigate the effect of a bouldering psychotherapy (BPT) on outpatients’ depressive symptoms compared with evaluated treatment options - namely mere physical activity (superiority analysis) and state-of-the-art cognitive behavioural therapy (CBT, non-inferiority analysis).

The results of the study may contribute to an enlargement of treatment options for outpatients suffering from depression. As bouldering is getting increasingly popular, participation in a bouldering therapy might be more socially accepted and thus may represent a lower threshold-offering than participation in classical psychotherapeutic approaches.

Participants of the study will probably benefit, as they receive additional therapy without incurring additional costs or wait times. All study arms were demonstrated to be effective in the treatment of depression prior to this study. Participants are free to start any additional treatments offered by the German health care system while participating in this study without suffering any disadvantages from study personnel, and patients’ individual ongoing treatment plans are not altered by their participation in this study.

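### The primary analysis sets are the wrong way round: per protocol decides superiority over EP, and intention to treat alone decides non-inferiority to CBT

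*Protocol article*

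**What the plan says.** The article has two confirmatory hypotheses: BPT is superior to the home-based EP (Hypothesis I), and BPT is non-inferior to group CBT (Hypothesis II). Data analysis assigns the deciding sets in one sentence: "The primary data analytic strategy is “per protocol” for the superiority trial and “intention to treat” for the non-inferiority trial". A literature reference is attached, but no reason is given. The next sentence adds, as a sensitivity analysis, that "an additional analysis with “intention to treat” for hypothesis 1 and “per protocol” for hypothesis 2 will be performed". Because this second sentence mirrors the first and names the hypotheses by number, the assignment is deliberate and cannot be read as a slip. No other section changes it.

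Three further statements bear on the point. Data analysis says that patients who drop out but can still be reached are interviewed. Under Interventions, BPT is a weekly group led by therapists, whereas EP is done alone at home, and "After 10 weeks, participants are asked how often they conducted the exercises". The Discussion says: "Participants are free to start any additional treatments offered by the German health care system while participating in this study".

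**The concern.** In a superiority comparison, randomisation protects the result only if patients are analysed as allocated. A per-protocol set selects on behaviour after randomisation. Here that behaviour differs in kind between the arms: attending a supervised weekly group, or keeping up unsupervised exercise at home. The patients left in each arm need not be comparable, and the planned regression adjustment (demographics and outside treatment) does not address why patients failed to adhere.

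In a non-inferiority comparison the usual worry is reversed. Patients who do not take up their allocated treatment tend to make the two arms look alike, and looking alike counts as success. Intention to treat as the only deciding set therefore lacks the safeguard that per protocol would supply.

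At stake is which result stands as the prespecified conclusion if the two sets disagree. As written, it is the less protective set for each hypothesis.

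**Working it through.** **1. The plan's own sample sizes (Sample size estimation).**
- Hypothesis I: "a slightly lower effect size of 0.6 was assumed", and "61 patients will be needed in the BPT group and 61 patients in the EP group (alpha = .05, power = .9". With two-sided 5% and 90% power, n = 2 × (1.960 + 1.282)² / 0.6² = 58.4, so 59 per arm (59.4, so 60, with the t distribution). This agrees with the stated 61 to within 2.
- Hypothesis II: margin 1.9 PHQ-9 points, SD 3.8, so 1.9 / 3.8 = 0.5 SD. With one-sided 5%, n = 2 × (1.645 + 1.282)² / 0.5² = 68.5, so 69 per arm, as stated. One-sided 2.5% would need 85. The article does not state sidedness, so one-sided 5% is inferred from this match.
- Total: 61 + 69 + 69 = 199, and 199 × 1.2 = 239, as stated.

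None of these figures depends on the choice of analysis set.

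**2. Hypothesis I: shift between the two sets.** If a share p of an arm is excluded, and those patients would have done g SD worse than the adherers, that arm's per-protocol mean improves by p × g. The shift in the BPT advantage is (p_BPT − p_EP) × g. Assumed: g = 0.25 to 0.75 in both arms.

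| Excluded from BPT | Excluded from EP | Shift (SD; + favours BPT) |
|---|---|---|
| 20% | 0% | +0.05 to +0.15 |
| 20% | 20% | 0 |
| 20% | 30% | −0.025 to −0.075 |
| 20% | 40% | −0.05 to −0.15 |

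Against the planned 0.6 SD, a shift of 0.05 to 0.15 is 8% to 25%, in either direction.

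**3. Hypothesis II: error under intention to treat alone.** Suppose BPT is worse than CBT by the full margin m (in SD) among adherent patients, and a fraction f of that difference is lost through non-adherence. The standard error with 69 per arm is √(2/69) = 0.170 SD. The chance of declaring non-inferiority is Φ(f × m / 0.170 − 1.645). With f = 0.2 (assumed):

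| Margin | Source | f × m / 0.170 | Error, one-sided 5% | Error, one-sided 2.5% |
|---|---|---|---|---|
| 0.2 SD | MADRS, lower | 0.235 | 7.9% | 4.2% |
| 0.34 SD | MADRS, upper | 0.399 | 10.6% | 5.9% |
| 0.5 SD | PHQ-9, 1.9 points | 0.587 | 14.5% | 8.5% |

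For the PHQ-9 margin at one-sided 5%, f = 0.1 gives 8.8% and f = 0.3 gives 22.2%.

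**4. What intention to treat does to power for Hypothesis I.** With the 20% allowance, 61 × 1.2 = 73 per arm. If a share f of patients contributes no difference between arms, the effect becomes 0.6 × (1 − f), and power is Φ(0.6 × (1 − f) / √(2/73) − 1.960):
- f = 0.1: effect 0.54, power 90%
- f = 0.2: effect 0.48, power 83%
- f = 0.3: effect 0.42, power 72%

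Per protocol with 61 per arm and the full 0.6 gives 91%.

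**The case against.** A reader might infer that both choices push the result towards BPT. The documents do not support that. Per-protocol bias for Hypothesis I can take either sign, and because EP is unsupervised, heavier exclusion there is plausible, which would work against BPT. What stands is that the primary superiority result would not be a randomised comparison, whichever way it errs.

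A reader might also infer that free access to outside treatment makes intention to treat the weaker set for Hypothesis II. It does not separate the two sets. Outside treatment is allowed, so starting it is not a protocol deviation, and nothing says that per protocol would remove those patients. Any dilution from that source affects both sets, and the fix below does not cure it. Nor does the 20% dropout allowance by itself pull the arms together, since reachable dropouts are still interviewed. The argument rests on non-adherence alone.

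The article does not define the per-protocol set. That definition may sit in a fuller document, so it cannot be assumed that attendance or the EP exercise question decides membership.

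The error rates in step 3 take the difference under full adherence as the target. Against the difference as it occurs in all randomised patients, the intention-to-treat test keeps its nominal level, and a naturalistic trial may well care about that difference. This is a reason to keep intention to treat for Hypothesis II, but not to let it decide alone.

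Finally, both sets are prespecified for both hypotheses, so readers would see all four results. That limits the harm without settling which result decides.

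**Conclusion.** The assignment is wrong as written. Hypothesis I would be decided on a subset selected after randomisation, and Hypothesis II on a single set that non-adherence can dilute towards no difference.

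For Hypothesis I the size is uncertain and the direction open: in the scenarios shown, between −0.15 and +0.15 SD, resting on assumed exclusion rates and an assumed gap between adherers and non-adherers. For Hypothesis II, a nominal 5% error becomes about 8% to 15% across the three fixed margins. This rests on an assumed 20% dilution, an inferred one-sided 5% and 69 analysed per arm. The 14.5% figure belongs to the PHQ-9 margin; for the main outcome, the MADRS, the figures are 7.9% and 10.6%.

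The case for the change rests on which set protects each conclusion, not on a demonstrated bias in favour of BPT.

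**What to change.** In Data analysis:
- **Hypothesis I:** make intention to treat (all randomised patients, as allocated) the primary set, with per protocol as the sensitivity analysis.
- **Hypothesis II:** claim non-inferiority only if the confidence bound lies inside the margin in both the intention-to-treat and the per-protocol sets.

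The change is one of wording, because both sets are already planned for both hypotheses and reachable dropouts are already interviewed. It has two costs. The chance of a positive Hypothesis II falls somewhat, since two sets must agree. Power for Hypothesis I may also fall below the planned level, as step 4 of the working shows, and should be checked against the non-adherence expected.

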#### Hypothesis I: superiority of BPT over EP

The primary outcome variable is the MADRS. To test the first hypothesis, t-tests for independent groups of change scores (pre-post) will be performed between the BPT and EP groups. In addition, multivariate analyses (ANOVAs and multiple linear regression analyses) will be calculated. To control for the effects of confounders, demographic variables as well as other therapeutic treatments patients used outside of the treatments offered in the study (e.g. antidepressive medication, psychotherapy, offers to participate in additional sports) will be included in the regression analyses.

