**Methods:**

The study is being conducted as a multicentre randomised controlled intervention trial at three locations in Germany. Participants are being randomised into three groups: BPT, CBT, or EP, each with a 10-week treatment phase. A power analysis indicated that about 240 people should initially be included. The primary outcome of the study is the Montgomery and Asberg Depression Rating Scale (MADRS) directly after the intervention. Additional measurement points are located three, six, and 12 months after the end of the intervention. The data are being collected via computer-assisted telephone interviews. Statistical analyses comprise regression analyses to test for the superiority of BPT over EP. To test for the non-inferiority of BPT and CBT, a non-inferiority margin of 1.9 points in the Patient Health Questionnaire (PHQ-9) and two non-inferiority margins for the MADRS (half of the two smallest Cohen’s d values from the current meta-analyses) was predefined. The mean difference between CBT and EP is being used as a supplementary equivalence margin.

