#### Inclusion and exclusion criteria

To increase external validity, only a few inclusion and exclusion criteria are being applied. *Inclusion criteria* consist of acute depressive symptoms, informed consent to participate in the study (especially regarding randomised allocation and data acquisition), and the ability to reach the therapy locations. The presence (or absence) of depression is operationalised as a PHQ-9 score of at least 8 points, ensuring a high level of sensitivity to all depressive disorders [37]. *Exclusion criteria* are age younger than under 18 years, a Body Mass index (BMI) under 17.5 or over 40, contemporary participation in another psychotherapeutic group therapy, started taking psychiatric medication within the last 8 weeks (medication started before 8 weeks is not a reason for exclusion), started individual psychotherapy within the last 8 weeks (same as for medication), a planned inpatient stay during the intervention period, physical contraindication for bouldering (physical disorders or pregnancy), specific psychiatric disorders (psychosis within the last 5 years, a manic episode within the last 5 years, substance addiction with substance abuse within the last year, Borderline diagnosis with self-harming behaviour during the last year), and acute suicidality. If it turns out that someone is in a suicidal crisis, appropriate steps following good clinical practice and a suicide risk management plan should be taken by the study personnel, if necessary by arranging for inpatient admission. For safety reasons, all participants are obliged to sign an anti-suicide contract for the duration of the study. All inclusion and exclusion criteria are assessed via self-reports with the screening questionnaire. In cases of unclear fulfilment of the inclusion or exclusion criteria (especially regarding relevant psychiatric diagnoses), potential participants are personally interviewed by the study personnel.

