### Randomisation

All individuals meeting the inclusion criteria in one study region are being randomised into one of the three groups (BPT, CBT, EP). Randomisation is stratified by sex and severity of depression according to the PHQ-9 score from the screening questionnaire (9–14 mild, 15–19 moderate, 20–27 severe depression). After randomisation, participants are informed about their allocation and provided with all necessary information about group participation. Randomisation is performed with a computer-based system by the Institute of Medical Informatics, Biometrics, and Epidemiology (IMBE) of the Friedrich-Alexander-Universität Erlangen-Nürnberg.

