#### Other measures

##### Screening questionnaire

The screening questionnaire is filled out by individuals interested in participating in the study after attending the informational sessions for the purpose of assessing the inclusion and exclusion criteria. It consists of sociodemographic data such as age and gender as well as open questions that reflect the criteria for inclusion and exclusion (e.g. height and weight to calculate BMI, current therapeutic treatment, physical limitations, psychiatric comorbidities, and depressive symptoms as assessed with the PHQ-9).

The following data are being assessed via the CATIs in addition to the questionnaires presented above*:*

*Sociodemographic data* (e.g. family status, level of education).

Data regarding *current occupation* (e.g. ability to work, current sick-leave status).

*Medical history regarding depression* (onset, duration, and progression of depression).

*Current therapeutic treatment* (medical, psychological, and drug treatment as well as inpatient treatment).

*Critical life events* during the past 6 months (e.g. death of a relative).

*Physical activity* (frequency and kind of activity beyond activities included in the study).

*Attitude towards physical activity* (positive or negative attitude).

*Attitude towards future group allocation* (EP, CBT, BPT, comfortable, uncomfortable, no preference)

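### Hypothesis I rests on an unadjusted change-score t-test, and the additional regressions do not limit outside-treatment covariates to baseline, so use begun after randomisation can enter the model

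*Protocol article*

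**What the plan says.** The section on Hypothesis I in the protocol article makes MADRS the outcome and states that "t-tests for independent groups of change scores (pre-post) will be performed between the BPT and EP groups". It continues: "In addition, multivariate analyses (ANOVAs and multiple linear regression analyses) will be calculated". To control for confounding, the regressions are to include demographic variables and "other therapeutic treatments patients used outside of the treatments offered in the study (e.g. antidepressive medication, psychotherapy, offers to participate in additional sports". No time point is attached to these treatments. Baseline MADRS and PHQ-9 severity are not named as covariates.

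The Methods paragraph of the abstract mentions no t-test: "Statistical analyses comprise regression analyses to test for the superiority of BPT over EP".

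Three other places bear on the point:

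- Randomisation: "Randomisation is stratified by sex and severity of depression according to the PHQ-9 score from the screening questionnaire". Under Study design and setting, allocation takes place within region and wave.
- Inclusion and exclusion criteria: recent starters of psychiatric medication or individual psychotherapy are excluded, but "medication started before 8 weeks is not a reason for exclusion". Some patients therefore enter with established treatment.
- Discussion: "Participants are free to start any additional treatments offered by the German health care system while participating in this study". Current treatment ("medical, psychological, and drug treatment as well as inpatient treatment") is recorded in the telephone interviews, and the screening questionnaire also asks about it.

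**The concern.** There are three linked issues.

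**Precision.** MADRS is measured at t0 and t1, and the stratification factors are known at allocation. A t-test on change scores implicitly fixes the baseline coefficient at 1 and ignores the strata. An ANCOVA estimates that coefficient and can include the strata.

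**Covariates.** In a randomised comparison, treatment begun after allocation is not a confounder. It can be a consequence of allocation, of worsening, or of both. Patients know their arm, so different uptake by arm is plausible. One listed covariate, additional sport, could even lie on the treatment's own pathway, since the Background suggests that climbing may help a person become more active. Conditioning on such variables can move the adjusted difference away from the effect of the assigned treatment.

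**Which result decides.** If the t-test and an adjusted regression disagree, the abstract and the analysis section point to different answers.

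**Working it through.** **1. The plan's own figure.** Inputs from Sample size estimation: d = 0.6, alpha .05, power .9, 61 per arm. Two-sided normal approximation: n = 2(1.960 + 1.282)²/0.6² = 58.4, so 59 per arm. The exact t-test needs 59.35, so 60, and power at 61 is 0.908. A one-sided test would need 48. The stated 61 is therefore reproduced to within two patients as a two-sided test. The article does not say whether d = 0.6 refers to the SD of the change score or of the t1 score.

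**2. Precision.** Let s be the SD of MADRS, assumed equal at t0 and t1, and r the t0-t1 correlation. The documents do not give r, so a range of 0.3 to 0.7 is assumed.

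- Change-score variance: 2(1 - r)s²
- ANCOVA variance: (1 - r²)s²
- Ratio: (1 - r²)/[2(1 - r)] = (1 + r)/2

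| r (assumed) | Change score / s² | ANCOVA / s² | Ratio |
|---|---|---|---|
| 0.3 | 1.40 | 0.91 | 0.65 |
| 0.5 | 1.00 | 0.75 | 0.75 |
| 0.7 | 0.60 | 0.51 | 0.85 |

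The variance is 15-35% lower. That is worth 1/0.85 = 1.18 to 1/0.65 = 1.54 times the patients.

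Power at 61 per arm (normal approximation):

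| r (assumed) | d on change-score SD: t-test | d on change-score SD: ANCOVA | d on t1 SD: t-test | d on t1 SD: ANCOVA |
|---|---|---|---|---|
| 0.3 | 91.2% | 98.4% | 80.0% | 93.5% |
| 0.5 | 91.2% | 96.9% | 91.2% | 96.9% |
| 0.7 | 91.2% | 94.9% | 99.0% | 99.6% |

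If d was meant on the change-score SD, the t-test meets its target. If it was meant on the t1 SD and r is low, the t-test falls short and ANCOVA does not.

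**3. Adjusting for later treatment.** This is a simulation with 1,000,000 patients per scenario, and every parameter is assumed. The direct BPT effect is -0.60 SD. Latent severity has a coefficient of 0.5 on the outcome. Uptake of outside treatment depends on arm and, where marked, on severity (log-odds slope 1).

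| Uptake BPT / EP | Severity-driven | Outside-treatment effect | Difference, unadjusted | Difference, adjusted |
|---|---|---|---|---|
| 20% / 20% | no | -0.3 | -0.60 | -0.60 |
| 24% / 24% | yes | -0.3 | -0.60 | -0.60 |
| 10% / 40% | no | -0.3 | -0.51 | -0.60 |
| 19% / 33% | yes | 0 | -0.60 | -0.54 |
| 13% / 42% | yes | 0 | -0.60 | -0.48 |
| 13% / 42% | yes | -0.3 | -0.51 | -0.48 |

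The third row can be checked by hand: -0.60 + (-0.3)(0.10 - 0.40) = -0.51. Adjustment there enlarges the difference by 0.09 SD. In the severity-driven rows it shrinks the difference by 0.03 to 0.12 SD. With equal uptake nothing changes.

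**4. Abstract against analysis section.** The abstract assigns the superiority test to regression. The analysis section assigns it to the t-test and calls the regressions additional. The abstract also describes the outcome as MADRS directly after treatment, while the t-test uses change. This second difference disappears under ANCOVA: once t0 MADRS is in the model, the arm coefficient is the same for t1 MADRS and for change.

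**The case against.** The strongest case on the other side has five parts.

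- **A reader might infer that the regressions adjust for treatment taken after randomisation and are therefore biased.** The text does not say so. It gives no time point, and patients with established treatment are eligible. Adjusting for treatment ongoing at t0 is legitimate. The Discussion shows that later starts are possible, not that they will enter the model, and bias needs uptake to differ by arm. All of this stands, so the point is a risk left open by the wording.
- **The change-score t-test is sound.** It is unbiased under randomisation, and the stated sample size supports it on one reading of d. This stands; the issue is efficiency only.
- **A reader might see three methods as three chances to claim Hypothesis I.** That goes too far. The analysis section puts the t-test first, and a two-group ANOVA of change scores is the same test (F = t²). What remains is the mismatch with the abstract.
- **The primary analysis set for Hypothesis I is per protocol, so it does not estimate the effect of offering BPT in any case.** This is true, but the choice of set does not settle which covariates are admissible. Conditioning on later treatment is a separate problem in either set.
- **A full covariate list belongs in an analysis plan.** That is fair for the missing detail. It does not cover a covariate rule that is stated without a time limit, or two statements of the superiority test that differ.

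**Conclusion.** The point holds as a matter of efficiency and of an open-ended covariate rule; it does not show that the Hypothesis I test is invalid. The unadjusted t-test gives up a variance reduction of 15-35%, assuming r between 0.3 and 0.7 and equal variances at t0 and t1. Table 1 lists recruitment as complete, so the gain would be narrower intervals and more power, not fewer patients.

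The regressions can give a biased difference in either direction if outside treatment begun after randomisation is included and uptake differs by arm. The shifts of up to 0.12 SD, or 20% of the planned 0.6, rest entirely on assumed uptake and effects and are illustrations only. The abstract and the analysis section need to agree on the test that decides Hypothesis I.

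**What to change.** Before the data are analysed:

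1. Name one primary model for Hypothesis I: t1 MADRS on arm, t0 MADRS, sex, PHQ-9 severity stratum and region/wave. The change-score t-test can stay as a supporting analysis.
2. Use the severity stratum as it was actually applied at randomisation. Eligibility starts at a PHQ-9 score of 8 and the listed strata start at 9, so these passages must be reconciled. Recoding the lowest stratum as 8-14 is tempting, but it would assume how patients scoring 8 were handled, which the article does not say.
3. Restrict outside-treatment covariates to use recorded at t0. Report treatment started later by arm, descriptively, and do not adjust for it.
4. Make the abstract's account of the superiority test match, in any update and in the results paper.

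The cost is wording: the variables are already collected. The downside is that this changes the primary test after recruitment is listed as complete. The change must therefore be dated, justified and documented before the data are analysed.
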